### Trial design {8}

The presented trial is a parallel-group, two-arm superiority RCT to evaluate the efficacy of a peer-supported IMS intervention for patients with type 2 diabetes mellitus in Lower Austria. Peer support via IMS in addition to standard therapy is compared with stand-alone standard therapy.

Moderators play a central role in peer-supported IMS intervention because they initiate and moderate the IMS exchange and discussion. They are patients with several years of disease and therapy experience because they need personal and practical experience in order to provide supportive and credible coaching. All moderators receive prior training and guiding material (see {11a}). The moderators are supported by a dietitian at regular intervals and by other study team members if needed. One moderator is responsible for one IMS group consisting of 14 participants maximum.

The participants will be fully informed about all aspects of the trial and asked to sign a consent form. The participants will be randomized at a ratio of 1:1.

The duration of the intervention is 7 months, followed by a 7-month follow-up period. The intervention will be performed twice to expand the recruitment phase. During the follow-up, the intervention group is expected to use the IMS tool without guidance by health professionals and both groups receive standard therapy.

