### Intervention description {11a}

The intervention is developed and conducted by an interdisciplinary team. Dietitians and moderators play an active role in the operational process of the intervention.

Dietitians are part of the team that develops the training curricula and is responsible for the training of the moderators and participants. They will supervise all moderators once a month via online meetings. During these meetings, the dietitians support moderators, e.g., if specific knowledge concerning diabetes care is needed or in case of technical problems.

Moderators act as facilitators and coordinators but they do not give medical or disease-related advice. In order to moderate communication and exchange in the IMS group effectively and authentically, personal and practical disease-related experiences of the moderator and the readiness to share these experiences with the group are essential. Moderators receive 9 h of training on the content to be shared via IMS and communication strategies to facilitate group exchange, peer support and behavioral change.

Participation in the clinical trial will last 15 months (1 month training/first measurement, 7 months intervention, 7 months follow-up). 196 participants will be randomly assigned to one of two groups: the intervention group or the control group. Participants who are randomly assigned to the intervention group will attend a 2 h technical training in connection with the first measurement. In the course of this training, they will learn how to use the *mattermost* app. After this training, they will join a *mattermost* group (instant messaging service group) with a maximum of 14 people for 14 months (7 months guided and seven without guidance). For the first 7 months of the intervention, an empowerment-based IMS communication strategy for diabetes self-management peer support has been developed.

Moderators are provided with a detailed handbook on web-based diabetes-related content and communication strategies to share this content with the group.

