### Outcomes {12}

Data will be collected four times over a period of 14 months: at baseline (T0), 3 months after the start of the intervention (T1; T0+ 3 months), at the end of the intervention (T2; T0+ 7 months), and after the follow-up (T3; T0+ 14 months), including the following collection of biochemical, psychosocial, and behavioral parameters during all four data collection points.

The primary outcome is the level of HbA_1c_ [%] measured using TOSOH G8 (Sysmex Austria GmbH).

Secondary outcomes are:

Psychosocial parameters:

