Medication adherence will be measured using the “A14-scale” [59]: the A14 consists of 14 items of non-adherent behaviors phrased in a non-threatening and non-judgemental way using a five-item Likert scale with the endpoints “4” (never) to “0” (very often).Dietary behavior and alcohol consumption will be measured using a food frequency questionnaire (FFQ), which assess “dietary behavior” and “alcohol intake” during the past 4 weeks with 53 items and the endpoints “never” and “more than 4 times a day”.Physical activity will be measured using the “International Physical Activity Questionnaire Short Form” (IPAQ-SF) [60, 61]: the IPAQ-SF asks seven questions to assess “vigorous-intensity” and “moderate-intensity” physical activity as well as “walking” and “sitting.” Participants indicate the time in minutes or hours for each activity level. Based on this information, three levels of physical activity (low, moderate, high) are calculated and expressed in metabolic equivalent of task (MET) minutes per week.Diabetes self-management behaviors will be measured using the “Summary of Diabetes Self-Care Activities German” (SDSCA-G) [62]: the SDSCA-G focuses on the past 7 days related to the diabetes self-care activities “nutrition,” “physical activities,” “blood glucose testing,” “foot care,” and “smoking.” The SDSCA-G consists of 11 items and participants mark the number of days the mentioned behavior was performed on an eight-point Likert scale with the endpoints “0” (0 days) to “7” (7 days). While the first ten items are calculated to a score and four sub scores (diet, exercise, blood-glucose testing, foot care), the eleventh item focuses on smoking habits.Clinic and communication visits (health professional visits in the past 6 months, hospital stays in the past 6 months).

Biochemical parameters:

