## Statistical methods

### Statistical methods for primary and secondary outcomes {20a}

Data will be analyzed using IBM SPSS Statistics 26 or greater (IMB Corporation, Armonk, NY, USA). The significance level will be set at 5%. Generally, metric data will be checked for normal distribution using a histogram of each variable, as well as for skewness and kurtosis. To illustrate descriptive parameters, the arithmetic mean and the 95% confidence interval will be stated for metric data. Interval variables or nominal scaled variables will be shown as frequencies. Repeated measures ANCOVA will be used to compare the control and intervention groups concerning primary and secondary outcome parameters. Non-normal metric data will be analyzed using the Mann-Whitney *U* test, the Kruskal-Wallis signed rank test, or the Friedman-Test [73].

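### The six-month recall for clinic visits and hospital stays makes half of the T1 count pre-intervention time, so a constant effect would seem to grow between T1 and T2

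*Protocol article*

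**What the plan says.** The behavioral parameters in Outcomes {12} end with clinic and communication visits, defined as "health professional visits in the past 6 months, hospital stays in the past 6 months". The same section places the visits after baseline at "3 months after the start of the intervention (T1; T0+ 3 months), at the end of the intervention (T2; T0+ 7 months") and, for the last one, at 14 months after T0. It states that the data collection covers "biochemical, psychosocial, and behavioral parameters during all four data collection points", so the healthcare-use item is asked at T0, T1, T2 and T3.

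Data management {19} repeats a six-month recall for medical consultations. Nowhere does the article give another recall period for any visit.

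Trial design {8} fixes the exposure periods: "The duration of the intervention is 7 months, followed by a 7-month follow-up period". For the analysis, Statistical methods {20a} says: "Repeated measures ANCOVA will be used to compare the control and intervention groups concerning primary and secondary outcome parameters".

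**The concern.** A look-back of fixed length suits a schedule whose visits lie at least that far apart. Here the gaps between visits are 3, 4 and 7 months and the look-back is 6. The answer at T1 must therefore reach back before the intervention began.

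The repeated measures comparison reads the pattern of group differences over T1, T2 and T3. If T1 is only half exposed and T2 fully exposed, a rise in the group difference from T1 to T2 may come from the wording of the item and not from the intervention. A reader of the results would naturally take such a rise for a delayed or growing benefit.

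This item is the only count of healthcare use among the listed outcomes. The article also treats regular medical contact as part of self-management (Strategies to improve adherence {11c}), so the time course of the item is likely to be interpreted.

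**Working it through.** **Inputs.** Recall length L = 6 months (Outcomes {12}). Visits at v = 0, 3, 7 and 14 months (Outcomes {12}). Guided intervention from month 0 to 7, follow-up from month 7 to 14 (Trial design {8}). The article states no figure of its own to reproduce here.

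**Step 1: windows.** A visit at month v covers the interval from v - 6 to v.

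| Visit | Window (months from T0) | Before start | Guided | Follow-up |
|---|---|---|---|---|
| T0 | -6 to 0 | 6 | 0 | 0 |
| T1 | -3 to 3 | 3 | 3 | 0 |
| T2 | 1 to 7 | 0 | 6 | 0 |
| T3 | 8 to 14 | 0 | 0 | 6 |

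The six pre-intervention months at T0 are a proper baseline. The pre-intervention share at T1 is 3/6 = 50%.

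**Step 2: overlaps and gap.** For neighbouring visits, take the end of the earlier window minus the start of the later one.

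- T0 and T1: 0 - (-3) = 3 months shared.
- T1 and T2: 3 - 1 = 2 months shared (months 1 to 3).
- T2 and T3: 7 - 8 = -1, so month 7 to 8 falls in no window.

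**Step 3: effect on the group difference.** Assume that the intervention changes the visit rate by a constant d per month from month 0. Randomisation makes the expected difference before month 0 zero.

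- T1: 3 exposed months × d = 3d, or 3d/6 = d/2 per recalled month.
- T2: 6 exposed months × d = 6d, or 6d/6 = d per recalled month.

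The six-month count difference doubles from T1 to T2 although the effect on the rate never changes.

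**Step 4: how far this depends on the assumption.** The ratio of T1 to T2 rests on an immediate, constant effect. A weaker statement does not: whatever the shape of the effect, the expected T1 difference comes only from months 0 to 3. Call it D. The six-month window reports D/6 per recalled month, and a window of months 0 to 3 would report D/3. The first is half of the second in every case.

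**Step 5: sensitivity to the start date.** Intervention description {11a} describes participation as "1 month training/first measurement, 7 months intervention, 7 months follow-up", so T0 may precede the start by up to about a month. With a one-month lag and later visits timed from the start, the visits fall at months 0, 4, 8 and 15 after T0, and the windows are -6 to 0, -2 to 4, 2 to 8 and 9 to 15. T1 still holds 3 pre-start months (-2 to 1). T0 and T1 then share 0 - (-2) = 2 months, T1 and T2 share 4 - 2 = 2 months, and the gap is still 1 month (8 to 9). The conclusion does not change.

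**The case against.** The strongest defence is that a constant window is a deliberate choice. Equal six-month counts can be compared directly with baseline, and they do not vary with missed or rescheduled appointments. This stands as a real trade-off and is priced under the fix.

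A second defence is that the error at T1 is conservative. The pre-intervention months are balanced in expectation, so they cannot create a difference between groups where none exists. The expected difference in the T1 count, 3d, is also the same as with a window of months 0 to 3; the added months bring only noise, part of which the T0 report may explain. This stands for T1 alone. It does not answer the concern about the pattern over visits: once T1 and T2 enter one repeated measures comparison as equal six-month counts, the dilution at T1 appears as change over time. Adjusting for T0 does not restore the missing exposure.

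A reader might infer more than the article supports, on three counts.

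- **That total use is miscounted.** Adding T1 to T3 would give 14 + 3 + 2 - 1 = 18 recalled months for 14 actual ones. The article plans no such sum and no cost analysis, so this harm is hypothetical.
- **That the overlap invalidates T1 and T2 as repeated measures.** They share 2 of 6 months, which adds correlation between two values from the same person. That does not by itself invalidate the group comparison.
- **That the whole outcome is unusable.** T2 lies wholly within the guided phase and T3 wholly within follow-up, and the two do not overlap.

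**Conclusion.** The point holds, and it is confined to T1 and to comparisons over time that include T1. Half of the T1 window (3 of 6 months) precedes the intervention and repeats time reported at T0. Under an immediate and constant effect on the visit rate, which the article does not state and which is assumed here, the T1 group difference per recalled month is half of the T2 difference, and the repeated measures comparison would show an apparent growth of effect. The two shared months and the one uncovered month become a problem only if someone forms total use over the trial.

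The issue is minor. The outcome is secondary and belongs to none of H1 to H5, and neither HbA1c nor the sample size is affected. The arithmetic uses only figures in the article and survives a one-month shift of T0. It would no longer apply if the questionnaire handed out at T1 used a shorter recall than the article states.

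**What to change.** Keep the six-month recall at T0 as the baseline rate. At T1, T2 and T3, ask about visits and stays since the last study measurement that the participant attended; the planned windows are then months 0 to 3, 3 to 7 and 7 to 14. Their lengths sum to 3 + 4 + 7 = 14 months, so every month is covered once and no pre-intervention time enters after T0 (apart from any lag between T0 and the start). Analyse rates per month, or model counts with the actual observation time as an offset, and record the date of the last attended measurement for each person.

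The change rewords one questionnaire item and changes the denominator. It has four costs:

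- The windows are unequal (6, 3, 4 and 7 months), so raw counts cannot be compared across visits.
- Recall error may differ between visits for the same reason.
- Hospital stays will show more zeros in the short windows at T1 and T2.
- Recall at T3 is seven months instead of six, and longer after a missed visit.

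If the item has already been used and cannot be changed, compare the groups at T2 and T3 separately, and state that the T1 count is half pre-intervention time and that a rise from T1 to T2 is not evidence of a growing effect.

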### Participant timeline {13}

The flow diagram showing the participant timeline through the DiabPeerS study is presented in Fig. 1. The SPIRIT figure for this trial is given in Fig. 2.

**Fig. 1 Fig1:**
[figure not shown]
Flow diagram DiabPeerS

**Fig. 2 Fig2:**
[figure not shown]
SPIRIT figure DiabPeerS

### Sample size {14}

An a priori calculation was performed using G-Power [68] for the primary outcome variable HbA_1c_, using an ANCOVA at 5% level of significance and 80% power. Based on previous research, we assumed a small to medium effect size for group differences in HbA_1c_ means (partial eta squared = 0.05, which corresponds to an effect size *f* = 0.229) [69–71]. Considering a 30% dropout ratio, we will include 98 randomly assigned participants in each group (196 total). The intervention group will be subdivided into seven IMS groups made up of 14 participants and one moderator each. Therefore, nine moderators (seven plus two for the compensation of possible drop-outs) will be additionally recruited (205 persons in total, 196 participants plus nine moderators). Although the moderators will participate in the assessments, their data will not be included in the analyses.

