**Methods:**

A total of 205 participants with type 2 diabetes mellitus will be included and randomly assigned to an intervention or control group. Both groups will receive standard therapy, but the intervention group will participate in the peer-supported IMS intervention, additionally. The duration of the intervention will last for 7 months, followed by a follow-up of 7 months. Biochemical, behavioral, and psychosocial parameters will be measured before, in the middle, and after the intervention as well as after the follow-up.

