### Concealment mechanism {16b}

For the allocation of the participants, a simple urn-based randomization is carried out. For this purpose, an urn, in our case a digital card set, is filled with 196 cards. On 98 of them, it says “intervention group” and on 98 “control group.” A unique ID is assigned to each card. The participants draw the cards themselves. This gives them the feeling that they have made their own decision and makes it easier for them to accept it, even if they do not end up in the desired group.

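### With 30% dropout, 196 randomised leaves about 137 completers and roughly 76% power, not the stated 80%; the abstract also gives the randomised number as 205 instead of 196

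*Protocol article*

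**What the plan says.** The Sample size section {14} describes a G-Power calculation for HbA1c "using an ANCOVA at 5% level of significance and 80% power", with an assumed effect of "partial eta squared = 0.05, which corresponds to an effect size *f* = 0.229". It then makes the dropout allowance: "Considering a 30% dropout ratio, we will include 98 randomly assigned participants in each group (196 total". The number evaluable before that allowance is not given. Allocation is 1:1 (Trial design {8}: "The participants will be randomized at a ratio of 1:1").

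The same section explains the figure of 205 as "205 persons in total, 196 participants plus nine moderators", and says that the moderators' data stay out of the analyses. The Intervention description {11a} and Implementation {16c} also use 196, and in Concealment mechanism {16b} "an urn, in our case a digital card set, is filled with 196 cards", half for each arm. The abstract differs: "A total of 205 participants with type 2 diabetes mellitus will be included and randomly assigned to an intervention or control group".

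**The concern.** A dropout allowance is meant to leave enough participants for the stated power once the assumed loss has occurred. Here the significance level, power, effect size, dropout and final number are all printed, so the chain can be checked, and the last step does not follow from the others.

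At stake is how the primary result is read. If 30% are lost and the assumed effect is real, the chance of missing it is about 24%, not 20%. A null result would then be judged against a power that the design does not have under its own dropout assumption. The abstract adds a second problem: it overstates the randomised number by nine in the part of the article that is read most.

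**Working it through.** **Inputs**

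- Test: ANCOVA F test, two groups, 5% level (Sample size {14})
- Target power: 80% (Sample size {14})
- Effect: partial eta squared 0.05 (Sample size {14}), so f² = 0.05/0.95 = 0.0526 and f = 0.2294, which agrees with the printed 0.229
- Allocation: 1:1 (Trial design {8})
- Dropout: 30% (Sample size {14})
- Number of covariates: not stated; assumed to be 1. Taking 0, 1, 2, 3 or 5 gives the same required number.

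**Formula.** Power = P(F′ > critical value), where F′ is non-central F with 1 and N − 2 − (covariates) degrees of freedom and non-centrality λ = f² × N. The critical value is the 95th percentile of the central F.

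**Power by number analysed (one covariate)**

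| N analysed | Power, f = 0.2294 | Power, f = 0.229 |
|---|---|---|
| 137 | 0.760 | 0.758 |
| 151 | 0.7998 | 0.798 |
| 152 | 0.802 | 0.801 |
| 196 | 0.892 | 0.891 |

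The smallest number reaching 80% is 152, or 76 per arm.

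**Reproducing the plan's 196**

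- Multiplying by 1 + d: 152 × 1.3 = 197.6 and 151 × 1.3 = 196.3, so 196 is close to this route.
- Dividing by 1 − d: 152/0.70 = 217.1, or 218 with equal arms (109 each). This does not give 196.
- Normal approximation: 150 evaluable, giving 195 by the first route and 215 by the second.
- One-sided test: 119 evaluable, giving 155 or 170. Neither gives 196.

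**What 196 delivers at 30% dropout**

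- Completers: 196 × 0.70 = 137.2, so 137.
- Power: 0.758 to 0.760 (about 0.766 by the normal approximation).
- Largest dropout compatible with 80% power: 1 − 152/196 = 22.4%.
- Effect detectable with 80% power at 137: f = 0.241, partial eta squared 0.055.

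**The 205.** 196 + 9 = 205, and the card set holds 98 + 98 = 196. No allocation exists for the other nine, who are the moderators.

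**The case against.** The strongest objection is that 196 may come from a different calculation. Statistical methods {20a} plans a repeated measures ANCOVA, and Outcomes {12} schedules four measurements. In a repeated-measures calculation for the averaged group effect, two measurements correlated at 0.8, or three at 0.85, would require 137 participants, and 137/0.70 = 195.7, which rounds to 196. On that reading the allowance was applied correctly and only the report of it is incomplete. This cannot be excluded. But those correlations are assumptions: section {14} names an ANCOVA and gives neither a number of measurements nor a correlation. If such a calculation was run, the section misdescribes it and still needs correcting.

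The multiplication by 1.3 is likewise an inference. It is not exact from 152, and 98 also equals seven messaging groups of 14, so group size may have shaped the final number. This point stands, and the cause should be described only as consistent with that slip. The shortfall is the same whatever the cause.

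It is also fair that the loss is only about 4 points, that it arises only if dropout exceeds about 22%, and that power would be 89% with no dropout. But 30% is the protocol's own planning figure, so the stated power should hold there. Analysis by intention to treat does not close the gap: section {20c} describes replacement of missing questionnaire items, not of a missing HbA1c, and section {14} itself treats dropout as lost information.

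The 205 is an editorial slip with no effect on conduct, since the body of the article is consistent at 196.

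**Conclusion.** The concern holds. For the test, effect size and dropout that section {14} states, 196 randomised gives about 76% power, not 80%. Meeting the target would take 218 randomised, 22 more than planned; equivalently, 196 tolerates about 22% dropout instead of 30%. The abstract's randomised number is too high by nine.

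This rests on a single-endpoint ANCOVA with f = 0.229, a two-sided 5% test, equal arms, independent participants and no gain in power from repeated measurements, none being claimed in the calculation. The number of covariates makes no material difference. The size of the shortfall is moderate; that the printed figures disagree is certain.

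**What to change.** Keep 196 and restate section {14} along these lines: 80% power at f = 0.229 requires 152 evaluable participants (76 per arm); 196 randomised meets this if dropout is at most 22%; at the assumed 30% dropout, 137 remain and power is about 76%. If the stored G-Power output shows a repeated-measures calculation, report its number of measurements, assumed correlation and evaluable number instead, so that the route to 196 can be followed.

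In the abstract, replace the 205 randomised with 196 randomised participants plus nine moderators who are neither randomised nor analysed.

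The cost is a change of text. Recruitment, allocation and analysis stay as they are; the published power statement becomes less favourable. Holding 80% at 30% dropout would instead mean randomising 218, with 22 more cards in the allocation set.

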### Strategies to improve adherence to interventions {11c}

The intervention consists of a peer-supported IMS intervention in addition to standard therapy. Therefore, adherence of participants to the IMS intervention pertains mainly to the IMS strategy, the measurements, and the initial training sessions.

The first step to improve adherence is the holistic explanation of the trial to interested participants during the initial appointment [50, 51]. In this appointment, sufficient time is scheduled in order to enable comprehensive understanding concerning the trial among participants.

Those who have greater responsibility - the moderators - will be individuals participating in the disease management program “Therapie aktiv – Diabetes im Griff” (https://www.therapie-aktiv.at), which is provided by the Austrian Health Insurance Fund. Hence, they are already proven to be generally adherent and engaged in their disease management. These moderators will positively influence their group members through the role model effect.

A dietitian experienced in counseling will support the moderators if problems arise and they will supervise all moderators once a month via online meetings. During the supervision, the dietitian will reflect on the past month and discuss the next steps of the IMS strategy with the moderators. If necessary, the communication expert can provide further assistance during these meetings.

Furthermore, we expect an additional positive social effect: participants will identify with their *mattermost* group and, in the next step, with the DiabPeerS trial. Hence, they will be interested in a successful intervention and participate actively. Also, frequent personal contact between the central study staff (EH, MH, AEZ) and the participants throughout the whole trial (initial appointment, four measurements, supervision meetings) will support adherence [50].

The IMS strategy (see {11a}), the core element of this trial, aims to improve diabetes self-management. Taking into consideration that regular medical appointments and monitoring are central in diabetes self-management, we assume that this increasing competence will support adherence to intervention as well.

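### The sample size and the named ANCOVA treat participants as independent, although the intervention arm is delivered in seven moderator-led chat groups; if outcomes correlate within groups, standard errors are too small and power falls further

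*Protocol article*

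**What the plan says.** Allocation is individual (Trial design {8}): "The participants will be randomized at a ratio of 1:1". The sample size (section {14}) was computed in G*Power "using an ANCOVA at 5% level of significance and 80% power", with "partial eta squared = 0.05, which corresponds to an effect size" f of 0.229. With 30% dropout this becomes 98 per arm, 196 in total. The next sentence of {14} reads: "The intervention group will be subdivided into seven IMS groups made up of 14 participants and one moderator each". Group and moderator form a single cluster, since "One moderator is responsible for one IMS group consisting of 14 participants maximum" ({8}).

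The intervention description {11a} keeps controls on standard therapy without any chat group. It gives the moderator a central part in guiding the group and building trust. Section {11c} adds: "These moderators will positively influence their group members through the role model effect". It also expects members to identify with their group.

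The analysis (section {20a}) is: "Repeated measures ANCOVA will be used to compare the control and intervention groups concerning primary and secondary outcome parameters". The protocol mentions no ICC, design effect, group term or cluster-robust standard error.

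**The concern.** This is a partially nested design: randomisation is by person, but one arm is treated in groups. Members of an IMS group share one lay moderator and talk to one another for up to 14 months. A moderator who does well or badly can move up to 14 outcomes together. The repeated measures part of the ANCOVA handles correlation within a person over time, not correlation between people in the same group.

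If such correlation exists, the model understates the variance of the intervention-arm mean. Confidence intervals for HbA1c and the secondary outcomes are then too narrow, the superiority test for H1 rejects too often, and the trial has less power than {14} states.

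**Working it through.** **Inputs from the protocol.** Two-sided 5%, 80% power, partial eta squared 0.05, 30% dropout, 98 per arm, seven groups of 14. **Assumed.** ICC of 0, 0.01, 0.02, 0.05 and 0.10, on the scale of the ANCOVA residual; equal total variance in the two arms; dropout spread evenly over groups.

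**1. The plan's own figure.** f = sqrt(0.05/0.95) = 0.229, so d = 2f = 0.458 for two equal groups. The noncentral F calculation (1 numerator df, 0 to 3 covariates) needs 152 evaluable participants.
- 152 × 1.3 = 198, close to 196.
- 152 / 0.7 = 218, which is not.

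So 196 is reproduced approximately, with independent participants, no design effect, and dropout added as a multiple of 1.3.

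**2. Power before any clustering.** 196 × 0.7 = 137 completers. At f = 0.229 their power is 75.8%. The gap of about 4 points to 80% is a dropout-inflation error, separate from clustering.

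**3. Adding the groups.** At 30% dropout there are n = 68.6 per arm and m = 14 × 0.7 = 9.8 per group. The design effect applies to the intervention arm only:
- DE = 1 + (m − 1) × ICC = 1 + 8.8 × ICC
- Correct variance = DE/n + 1/n; variance assumed by the ANCOVA = 2/n
- SE ratio = sqrt((DE + 1)/2)
- Actual type I error = 2 × [1 − Φ(1.96 / SE ratio)]
- Normal power = Φ(0.458/SE − 1.96)
- Satterthwaite df = V² / [(DE/n)²/6 + (1/n)²/(n − 1)], where V is the correct variance and 6 = 7 groups − 1; power then from the noncentral t

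Example, ICC 0.05: DE = 1.44; SE ratio = sqrt(2.44/2) = 1.105; SE = sqrt(2.44/68.6) = 0.189; normal power = Φ(2.43 − 1.96) = 68%.

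| ICC | DE | SE ratio | Type I error, unclustered test | Power, normal | Power, Satterthwaite | df |
|---|---|---|---|---|---|---|
| 0 | 1.00 | 1.00 | 5.0% | 76.5% | 72.7% | 22 |
| 0.01 | 1.09 | 1.02 | 5.5% | 74.7% | 70.6% | 21 |
| 0.02 | 1.18 | 1.04 | 6.0% | 73.0% | 68.5% | 19 |
| 0.05 | 1.44 | 1.10 | 7.6% | 68.0% | 62.8% | 16–17 |
| 0.10 | 1.88 | 1.20 | 10.2% | 60.8% | 54.7% | 14 |

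**4. Simulation check.** 40,000 runs per setting, seven groups of 10 completers against 70 controls. For ICC 0.01 / 0.02 / 0.05 / 0.10, the unclustered type I error was 5.5 / 6.0 / 7.5 / 10.4%. Power of the group-respecting test was 71 / 69 / 63 / 55%, and its own type I error stayed between 5.0% and 5.3%.

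**5. No dropout at all.** With 98 per arm and m = 14, power under independence is 89%. With Satterthwaite df it is about 82% at ICC 0.02 and 74% at ICC 0.05.

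**The case against.** Four arguments on the other side have weight.

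*The ICC is unknown.* A reader might infer that the standard errors are certainly wrong. The protocol does not support that. At ICC 0 they are correct, and at 0.01 the test's error is only 5.5%. Expecting all moderators to help predicts a shift in the mean, not in itself variation between moderators. What stands against this is that the mechanism in {11a} and {11c} makes some variation plausible, and the protocol gives no reason to take it as zero.

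*The type I error depends on the null.* Allocation is individual. If the intervention affects nobody, group membership adds no correlation and the test stays near 5%. Inflation needs group effects that differ between moderators yet average to zero. This is right, and the type I figures hold only under that condition.

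*Not all of the power gap is clustering.* A reader might set 63% against 80% and blame the groups for everything. About 4 points come from the dropout inflation. About 4 more (76.5% to 72.7% at ICC 0) are the price of estimating variance from seven groups. Correlation itself then costs about 2 / 4 / 10 / 18 points. Without dropout, 80% is still met at ICC 0.02.

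*The model details may be in an analysis plan that is not shown.* It could add a group term. It could not change the basis on which {14} fixed the sample size, and the method {20a} names has no place for the groups.

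Sections {11a} and {16c} also speak of control teams or groups of 14. These share neither a chat nor a moderator, so nothing there suggests clustering in the control arm.

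**Conclusion.** The point holds in conditional form. The sample size and the named analysis both assume independent participants, while the intervention arm is treated in seven moderator-led groups. If outcomes correlate within groups, the reported standard error is too small. At 30% dropout and an assumed ICC of 0.01 to 0.10, the correct one is 2 to 20% larger. The unclustered test's error is then 5.5 to 10.2% under a zero average effect with varying group effects. Power of a group-respecting test is 75 to 61% by the normal approximation, or 71 to 55% with degrees of freedom for seven clusters. The benchmarks are both the stated 80% and the 76% delivered at ICC 0.

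The protocol does not support saying that the type I error necessarily exceeds 5%, or that clustering alone explains the missing power.

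**What to change.** In {20a}, analyse HbA1c and the continuous secondary outcomes with a linear mixed model that has:
- the within-person repeated structure already intended;
- a random effect for IMS group in the intervention arm only, with each control as a singleton;
- separate residual variances for the two arms;
- Satterthwaite or Kenward-Roger degrees of freedom.

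A cohort fixed effect is optional and not part of this error.

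In {14}, keep 196 and restate power as conditional on 30% dropout and on a declared ICC range that includes 0 and 0.01.

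The cost is protocol wording and a different SPSS procedure. Section {12} says the exported chat rooms correspond to the assigned groups, so membership is already recorded. Intervals become wider (SE about 2 to 20% larger, df about 14 to 21), the variance component from seven groups will be imprecise, and the stated power will look less favourable. Restating power does not restore it. By the normal approximation at 9.8 completers per group, 80% power would need about 226 / 235 / 263 / 309 randomised for ICC 0.01 / 0.02 / 0.05 / 0.10, with dropout handled as N/0.7. The change should be fixed before outcome data are examined by arm.
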